#### Natural maturation

will take place as each participant (adolescent and/or parent) becomes more familiar with the disease and treatment, which can potentially result in better satisfaction scores and outcomes. This aspect is dealt with in two ways. First, the crossover design with a randomized assignment of participants should decrease the risk of bias in the selection groups and result in similar distributions in each group. The adequacy of the follow-up durations for this study was determined in previous studies
[14,74].

#### Contamination

Is not expected as each TN consultation is done on an individual basis. However, if contamination where to occur, this would result in better outcomes in the control group and would consequently reveal an apparent null effect of the intervention. We do not expect the usual high standards of care and services to change as a result of the introduction of TN as the nurse who gives the TN consultation is self-employed and provides the service on a private individual basis. Furthermore, a mobile telephone number will be used for the TN service, different from the outpatient clinic’s number assigned to the control group. To further control risk of contamination, only newly diagnosed children will be recruited into the study; they will thus not have had the opportunity to develop any relationships with the staff currently working at the study site. Nevertheless, all changes in policies and documentation will be recorded during the study period.

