[43,69,73]. Two specialist nurses, each with more than 5 years experience in adult and pediatric rheumatology, will attend a three-day course to enhance their skills in verbal communication, strategies for questioning parents and adolescents, assessing the quality of interactions, and aiding decision-making. The telephone intervention process will be standardized and recorded for each participant. It will involve a comprehensive, systemic assessment of the participant’s needs, including basic elements such as the participant’s characteristics, the date, time, and nature of the call, as well as a detailed description of the symptoms, problems, or reasons for the call. Following this assessment, prioritization and a plan will be developed collaboratively. Finally, the plan’s outcomes will be evaluated (was advice followed?).

Participants in the experimental TN group will attend a face-to-face medical and nursing consultation at baseline (T0) and then receive a monthly telephone call for 12 months. The face-to-face visit involves the TN nurse meeting with the parents and familiarizing herself with the child’s clinical, social, and family situation. The TN nurse will call the participant a total of 12 times, once during the last week of each month. Furthermore, the parent (and/or child if mature enough) will be given a telephone number (except for the control group) to call, as and when necessary, during normal Monday to Friday office hours. The TN nurse on duty will answer these calls and provide the same service.

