#### Control group

Children in the control group will receive the same standard care and services provided to all children and their families admitted to the rheumatology outpatient clinic. Children with rheumatic diseases attend several appointments here and are followed up at varying time intervals depending on the progress of their disease, but usually four times a year. Currently, the medical management of these children is provided mainly by a pediatric rheumatologist, but other specialists participate as determined by the child’s needs. Physiotherapists and occupational therapists are available and can refer patients to healthcare professionals outside the hospital.

At T0, control group participants will also have a face-to-face medical consultation at the pediatric rheumatology outpatient clinic, during which the study protocol will be clarified. The medical consultation will be repeated every three months as per current practice. Parents will be informed that they can call the outpatient clinic when necessary and speak a duty nurse. To avoid potential contamination between groups, control group parents will be assigned a telephone number other than the TN service number. Currently, duty nurses are clinical specialists in pediatrics with some rheumatology experience, but are not specifically trained in TN. The nature and frequency of all calls will be recorded in a logbook.

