### Data collection

Data will be collected at different time points over the 24-month study period (see Figure 
2). Participants switch to the other allocated group immediately after completion of study period 1. In this particular study, a wash-out period is considered unnecessary as the next measurement of satisfaction takes place six months after the start of period 2; this provides sufficient time to eliminate any residual effects of the treatment allocated in period 1. Data collection will be shared between the telephone nurses, a research assistant (nurse), and a physician. Telephone nurses will record the frequency, duration, and nature of all calls made and received. Records of each telephone call will be taken throughout data collection periods 1 and 2 (two years for each participant).The choice of the number of data collection points and the study timespan is based on theoretical and practical considerations
[74]. For practical reasons, patients will be enrolled in the first week of the month; face-to-face consultation baseline data (demographics, health status, and satisfaction) will be collected at this time (T0). Collection points occur every three months for assessments of disease activity and health status (T3, T6, T9, T12, T15, T18, T21, and T24) and every six months for the satisfaction questionnaire (T6, T12, T18, and T24).

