### Randomization and allocation of treatment

In crossover trials, both experimental and control experiments are given to every participant, randomizing the order in which they are applied
[65]. Consenting participants will be allocated treatment using a computer-generated simple block randomization. The benefits of using blocks are to ensure that the accrual of participants to either arm is uniform over time. An independent researcher, not involved in the recruitment or evaluation of follow-up, will prepare sealed, numbered envelopes containing an allocated treatment. Once randomization has occurred, blinding of participants and the caregiver is not feasible for this type of intervention, providing a potential risk for bias.

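### The grounds for expecting no contamination fit a parallel-group trial; here every period-2 control family has just had 12 months of telenursing and was given its number

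*Protocol article*

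**What the plan says.** The Contamination section says of contamination: "Is not expected as each TN consultation is done on an individual basis". It adds that "a mobile telephone number will be used for the TN service", distinct from the clinic's own number, and that newly diagnosed families have had no chance to form ties with clinic staff. It accepts that contamination, if it happened, would improve control outcomes and could make the intervention look ineffective.

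Other sections set out who the controls are:

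- Randomization and allocation of treatment: "both experimental and control experiments are given to every participant, randomizing the order in which they are applied".
- Data collection: "Participants switch to the other allocated group immediately after completion of study period 1". Also: "a wash-out period is considered unnecessary as the next measurement of satisfaction takes place six months after the start of period 2".
- Intervention: "The TN nurse will call the participant a total of 12 times, once during the last week of each month". The parent, or a mature child, "will be given a telephone number (except for the control group) to call, as and when necessary".
- Control group: "control group parents will be assigned a telephone number other than the TN service number".
- Hypotheses testing: mixed effect linear models are to exclude carry-over and temporal effects.

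**The concern.** Each ground given in the Contamination section treats a family as belonging to one arm for the whole study. Under the crossover, the TN-first families become controls at T12. By then they know the TN nurse, have had her information and decision support, and were given her number. The section does not mention them.

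Their period-2 scores form the control side of the within-child comparison for one of the two sequences. If those scores stay raised because the benefit lasts or the service is still used, the two-period estimate shrinks. That is the bias the section itself describes. The within-child comparison is also the reason the Study design section gives for choosing a crossover.

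**Working it through.** **1. Which control data are affected.** There are two sequences, TN then control and control then TN. All controls in period 2 come from the TN-first sequence (28 of 28 as recruited, about 23 of 23 completers). All controls in period 1 are untouched by TN. So 100% of period-2 control data, and 50% of all control observations, follow TN.

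**2. Whether the safeguards reach these families.**

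| Safeguard | Period-1 controls | TN-first families after T12 |
|---|---|---|
| Individual consultations | Limits spread between families | Does not address spread within a family over time |
| Separate number | Never given the TN number | Assigned another number, but no section withdraws the first |
| No earlier relationship | Concerns clinic staff | 12 monthly calls with the TN nurse |
| Six months before the next score | Not relevant | Asserted without data; addresses fading of a past effect, not continuing access |

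**3. The plan's own figure.** Inputs from Sample size and power: 70% against 20% scoring ≥ 30, two-sided alpha 0.05, power 0.90.

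n = [1.960·√(2 × 0.45 × 0.55) + 1.282·√(0.70 × 0.30 + 0.20 × 0.80)]² / 0.50² = 18.6, so 19 per group.

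With continuity correction: (18.6/4)·[1 + √(1 + 4/(18.6 × 0.50))]² = 22.5, so 23 per group. This matches the stated 23. Power at 23 per group is 0.953 without the correction and 0.913 by Fisher's exact test. The sizing is a comparison of two separate groups.

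**4. Effect on the two-period estimate.** Let L be the share of the 50-point effect that persists or stays accessible in the TN-first control period. L is an assumption; the article gives no value. Taking the planned rates:

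- TN-first: 70 − (20 + 50L) = 50 − 50L
- Control-first: 70 − 20 = 50
- Average of the two: 50 − 25L

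An additive period effect cancels in this average, but L does not. The period-1 comparison stays at 70 − 20 = 50 for any L.

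| L | Pooled control rate | Difference (points) | n per group, corrected | Power, 23 per group | Power, 46 per condition |
|---|---|---|---|---|---|
| 0 | 20% | 50 | 23 | 0.953 | >0.99 |
| 0.25 | 26.25% | 43.75 | 30 | 0.869 | 0.994 |
| 0.5 | 32.5% | 37.5 | 41 | 0.736 | 0.961 |
| 0.75 | 38.75% | 31.25 | 58 | 0.570 | 0.865 |
| 1 | 45% | 25 | 88 | 0.400 | 0.685 |

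Power is uncorrected. The last column counts all 46 completers once under each condition and treats the observations as independent, which is approximate.

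**5. The other direction.** If losing TN lowers satisfaction, L is negative. The control rate cannot fall below 0%, so L ≥ −20/50 = −0.4, and the difference could rise to at most 50 + 25 × 0.4 = 60.

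**6. Whether the mixed model removes it.** With two sequences and two periods, carry-over is confounded with sequence and with treatment-by-period interaction. A model that assumes no carry-over estimates 50 − 25L. One that allows freely for it has, in essence, only the period-1 comparison left to estimate the TN effect.

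**The case against.** The strongest reply is that the Contamination section concerns spill-over between families and to clinic staff, while residual effects within a family are treated under Data collection and Hypotheses testing. The separate-number rule, read with the switch at T12, applies on its face to TN-first families too. Calls are already recorded in both periods, so a control-period call to the TN nurse would be captured. Handling of the TN line after the switch is operational detail that an article may leave to the full protocol.

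Part of this stands. The logging exists and need not be added. The article allows that contamination might occur and states its consequence. Continued use of the TN line in period 2 is neither stated nor ruled out. The quantity L does not separate access from ordinary carry-over, so the table is no evidence for access as such.

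The statement about contamination still fails. It is made without qualification for the whole trial, and its reasons do not reach the families who supply every period-2 control score. Assigning a second number does not remove the first.

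A reader might infer that the control arm is contaminated by design and the effect certainly diluted. The article does not support that: L is unknown, it may be zero, and a contrast effect could reverse the bias. A reader might also infer that period 1 must replace the crossover analysis as the main conclusion. That would give up the within-child comparison chosen because the disease is so heterogeneous, and the evidence does not require it.

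**Conclusion.** The point holds as a correction to the wording, with a cheap safeguard attached. The reasons given for expecting no contamination do not apply to the TN-first sequence in period 2, which supplies half of all control observations. Those data are exposed to contamination and carry-over. The six-month argument rests on no data, and the planned model cannot exclude the effect.

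The possible size is 25L points off a planned 50, from none at L = 0 to 25 at L = 1, with up to 10 points in the opposite direction if losing TN lowers scores. This rests on the planned 70% and 20%, equal sequences, additive effects and an undocumented L. Bias in the estimate is the firmer worry: with all 46 completers counted under both conditions, approximate power is still 0.961 at L = 0.5.

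**What to change.** 1. In the Contamination section, limit the claim to families not yet exposed to TN, and say that TN-first families in period 2 are a recognised route for contamination and carry-over.
2. State that from T12 these families' calls to the TN number are passed to the clinic line, which is what the separate-number rule in the Control group section intends.
3. Flag control-period contacts with the TN nurse in the call records already kept, and report their number.
4. Prespecify the period-1 between-group comparison (T6, T12) as a sensitivity analysis, reported beside the two-period estimate. It is free of this problem and matches the sizing of 23 per group.

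The cost is a few sentences, one flag in an existing log and one further analysis. The period-1 estimate lacks within-child precision, which is why it should accompany the crossover analysis and not replace it.

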### Data management

#### Data quality

To ensure data quality, the research assistant will verify that all research forms have been completed at each data collection point of each data collection period. However, it is ultimately the Principal Investigator’s responsibility to ensure that appropriate work books and data sheets contain accurate and complete information.

#### Confidentiality and data security

Access to medical records will be limited to the research team and only with the approval of the Medical Director of the outpatient clinic. Measures to ensure data security and participant confidentiality will include: the removal of all identifying data and coding on the research forms; the storage of coded data on a password-protected computer with personal logins; access to data being limited exclusively to the research team; and data stored on paper or in recorded forms will be securely stored in a locked cabinet in the Principal Investigator’s office for a duration of 10 years after completion of the study
[89].

### Ethical considerations

The study and its amendment were approved by the Human Research Ethics Committee on January 17, 2011 and March 28, 2011, respectively.

Families who met the inclusion criteria received an information letter by post about the research study and were informed that it will be discussed at their next appointment with the medical specialist. They received verbal information about the study’s objectives, its procedures, potential risks, and their right not to participate or to withdraw at any time without this affecting the quality of future care. They were also informed of the measures taken by the researcher to ensure confidentiality, including that the participants will not be individually identified by name in reports or publications. Upon agreement to participation in the study, parents will be asked to provide written informed consent. Written assent will be obtained from children who are considered to have the capacity to make an ‘informed decision’ about the intervention (from 11 to 16 years).

## Discussion

The literature review highlighted the paucity of studies demonstrating strong evidence of the benefits of TN consultations for children with chronic conditions. However, nurse-led telephone follow-up interventions have shown positive effects on treatment adherence in adult populations with chronic illness
[90]. Treatment adherence to control children’s rheumatic diseases is crucial to limiting disability later in life. However, we know from the literature that when children enter adolescence, treatment adherence is poor, which may result in detrimental consequences
[91]. Support to parents and adolescents is crucial in this difficult transition phase. Our intervention was designed to provide information, affective support, and aid to decision-making. Although this intervention has been standardized, it allows for individualized care because it is tailored to the client’s characteristics and needs ensuring regular follow-up care. The intervention is very much dependent on the competence of the person providing the consultation. It is clear that this type of interaction requires advanced specialized skills, which is the case with the nurses involved in our TN study.

This study’s design has several strengths. First, the combination of quantitative and qualitative data for the primary outcome (satisfaction) will provide a better understanding of how and why the participants are satisfied with the service and will provide additional validity to the results. Second, the study is conducted in several centers, representing a large proportion of the population of interest in western Switzerland. Third, the processes put in place for the quality control of study protocol compliance should be highlighted. All telephone calls are recorded and a checklist ensures that all elements of the intervention are provided. Close study monitoring also provides important information about the feasibility of the study intervention in real life situations. Finally, the research is an attempt to meet the needs of the population of children and adolescents with rheumatic diseases in western Switzerland. This topic is of foremost importance because, health outcomes have become a priority for hospital-wide quality improvement initiatives and the Swiss Nursing Research Agenda.

Some limitations must be acknowledged, however. The intervention made by two experienced nurses may be difficult to replicate by others if the necessary training and formal education is not provided to nurses. To the best of our knowledge, this type of education is not offered in current postgraduate nursing programs. Finally, the JAMAR questionnaires have been validated in their original versions only. Psychometric equivalence has yet to be determined and the results of this study will contribute to the further psychometric testing of this questionnaire. However, the rigorous translation method and pre-test should have minimized the risk of a change in the psychometric properties of the questionnaires.

### Trial status

Recruitment for the trial started in August 2011 and follow-up data collection is due to complete in August 2014.

## Abbreviations

TN: Telenursing; PROC: Pediatric rheumatology outpatient clinic; JIA: Juvenile idiopathic arthritis; CTD: Connective tissue diseases; IMCHB: Interaction model of client health behavior; CSQ-8: Client satisfaction questionnaire-8; SSI: Semi-structured interviews; JADAS: Juvenile arthritis diseases activity score; JAMAR: Juvenile arthritis multidimensional assessment report; PARQ: Parent adherence report questionnaire; CARQ: Child adherence report questionnaire.
